## Abstract

**Introduction:**

Hypertensive disorders occur in approximately 10% of women during pregnancy. There is robust population-based data to show that women who have hypertension in pregnancy are much more likely to develop cardiovascular disease (CVD) in the postpartum period. Women with a hypertensive disorder of pregnancy (HDP) are twice more at risk of heart disease and stroke, and four times more likely to develop hypertension after birth. Two out of three women who had HDP will die from CVD. Recent evidence suggests that young women with HDP develop signs of CVD in the immediate postpartum period, rather than several decades later as previously presumed. If confirmed, this concerning finding presents healthcare practitioners with an opportunity to influence women’s cardiovascular health by advising on lifestyle choices and considering therapeutic interventions to prevent the development of CVD.

**Methods and analysis:**

This prospective cohort study design will ask approximately 300 participants to complete 3 days of home blood pressure monitoring every fortnight for 12 weeks postpartum and will culminate with a 24-hour episode of ambulatory blood pressure monitoring at 12 weeks postpartum. Women and healthcare professionals will complete questionnaires surrounding postpartum care for women who had HDP and knowledge of CVD risk. In addition, the relationship between hypertension and factors likely to influence outcomes such as severity of HDP, maternal age, body mass index and ethnicity will be analysed using logistic regression. Blood pressure and data from questionnaires will be analysed using descriptive statistics, with temporal stratification.

**Ethics and dissemination:**

Research ethics approval was obtained from London-West London & GTAC Research Ethics Committee. Research outputs will be published and disseminated through midwifery, obstetric or general practitioner targeted academic journals. The patient and public involvement group will disseminate findings to women who have experienced HDP among their peer groups.

**Trial registration number:**

NCT05137808.

Strengths and limitations of this studyThis is the first study to our knowledge exploring the recovery of blood pressure longitudinally in the immediate postpartum period after gestational hypertension.Home blood pressure monitoring will be compared against the gold standard; ambulatory blood pressure monitoring.Self-monitoring and reporting of blood pressure measurements by research participants may introduce the challenge of missing data.

## Introduction

Hypertensive disorders of pregnancy (HDP) affect approximately 10% of pregnant women.^1^ The most serious of these disorders is pre-eclampsia which affects 3%–5% of pregnant women worldwide. Aside from chronic or pre-existing hypertension which predates pregnancy, gestational hypertension and pre-eclampsia can occur at any point in pregnancy and early postpartum period from 20 weeks gestation.^1^ Women who experience HDP are at increased risk of cardiovascular disease (CVD), hypertension, diabetes, renal disease and stroke in their future life.^1 2^ Hypertension is the leading risk factor for CVD in the UK^3^ and it can be identified as early as the immediate postpartum period.^4–6^ Recent evidence suggests that young women are developing signs of CVD immediately in the postpartum period after HDP, rather than several decades later than previously presumed.^6 7^

CVD is largely preventable with simple lifestyle modifications and treatment.^8^ If postpartum women with a history of HDP engaged in healthy lifestyle activities (moderate exercise, reduced alcohol consumption, stopped smoking, healthier diets, reduce time watching television and maintained a healthy body mass index <25), they could reduce their risk of CVD by up to 92%.^9^

There is currently no standard monitoring for CVD development postnatally for women who had HDP, unlike their counterparts—women who develop gestational diabetes (GDM). Women with GDM are at increased risk of type 2 diabetes in later life. In the postpartum period, general practitioners (GPs) assess fasting blood glucose and/or haemoglobin A1c to identify the development of type 2 diabetes for women who had GDM and they will receive this annually.^10^ Women who have HDP currently do not receive this level of monitoring for the development of CVD. This study seeks to address this disparity by assessing the prevalence of postnatal hypertension, which may highlight the need for monitoring of CVD development.

The gold standard for diagnosing hypertension is 24-hour ambulatory blood pressure monitoring (ABPM).^11^ However, home blood pressure monitoring (HBPM) is becoming more widely used in maternity care, particularly in the antenatal period since the COVID-19 pandemic^12^ and more recently, self-management of BP in the postpartum period has been considered.^13^ To add to this expanding evidence-base, this study will assess the accuracy of HBPM versus ABPM and if there is a role for HBPM in the postnatal period for diagnosing hypertension.

This study will highlight the proportion of women with persistent hypertension from week 2 to 12 postpartum and whether these women share common characteristics such as raised body mass index and/or maternal age. This is valuable information for clinicians so they know which women are at higher of risk of uncontrolled hypertension and require closer blood pressure (BP) surveillance. The current national guidance for monitoring BP in the postpartum period is minimal and this research will therefore ascertain if the national guidance for monitoring hypertension^14^ in the postpartum period is sufficient. It will highlight if women who had HDP need further monitoring of hypertension between week 2 and week 8 postpartum and therefore highlight the important timelines for monitoring BP and the need for therapeutic intervention to control BP.

This study will ascertain if the HCPs involved in the care of women who may at be at increased risk of CVD due to developing HDP are educated about the risks and approaches to monitor for CVD. Roth *et al* undertook a systematic review assessing knowledge gaps of women and HCPs around CVD risk and HDP.^15^ The authors concluded that there was a low level of knowledge among women and HCPs concerning CVD risk and HDP. If HCPs and women are not educated about the risks, the path to significant heart disease is expedited. The postnatal period presents an optimum time for women to be receptive to change and lifestyle modifications,^16^ with opportunities for HCPs to influence positive change.

The main objective of this prospective cohort study is to observe the recovery (or lack thereof) of maternal hypertension from week 2 to week 12 after a pregnancy affected by new onset of hypertension and identify the prevalence of persistent postpartum hypertension in this cohort of women. A secondary objective will be to assess the accuracy of HBPM in comparison with ABPM to inform if HBPM can be used as an alternative method for diagnosing hypertension in the postpartum period. Other outcomes of interest will include women’s self-reporting of their 6-week to 8-week GP postnatal review, their perceived risk of developing CVD associated with HDP, their emotional well-being and their views on HBPM and ABPM. These objectives will be assessed via online questionnaires distributed at 8 and 12 weeks post partum, respectively. In addition, healthcare professionals involved in the postnatal care of women with HDP will receive an online questionnaire assessing their knowledge on HDP and associated CVD risk.

## Methods and analysis

### Recruitment and sampling

Participants will be recruited across three NHS maternity sites in South England. Potential participants will be approached during the antenatal and postnatal period before discharge home if they have been identified as having new onset of hypertension in pregnancy by way of convenience sampling. Recruitment will commence in April 2022 until March 2023 and all data collection will cease in June 2023 allowing 12 weeks of BP monitoring from when final participants were recruited in March 2023.

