### Inclusion and exclusion criteria

Eligible research participants will require a diagnosis of new-onset hypertension in pregnancy after 20 weeks gestation and up to 72 hours postpartum. Research participants in whom English is not their primary spoken language must demonstrate evidence of the ability to communicate any abnormal BP readings with their healthcare provider.

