### Data collection

#### Home blood pressure monitoring

Research participants will undergo HBPM every fortnight from week 2 post birth until week 12 as per a HBPM protocol based on that used by Alemida *et al*. Women will take three BP readings in the morning, early afternoon and in the evening, a total of nine BP readings per day, for three consecutive days.^17^ At week 12, women will undergo 24-hour ABPM (figure 1).

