### Data analysis

#### Objective 1: to identify which BP will be used to calculate the rate of persistent hypertension at 12 weeks postpartum

The first and second BP readings will be compared with the third reading to assess if they vary by >10/5 mm Hg. The mean or median of all BPs will be used if no significance is found or the third BP reading will be used for interpretation if there is a significant difference (>10/5 mm Hg) between BPs. The BP taken at three time periods (morning, midday and evening) will also be analysed to assess if findings vary significantly by >10/5 mm Hg. If no significance is found, the mean or median BP readings for the day will be calculated and used for further analysis. If significant difference found, each time period will be compared with daytime ABPM to see which time point mostly correlates with daytime ABPM. This will be analysed using one sample t-test of the difference and intraclass correlation co-efficient (ICC).

Using descriptive statistics, HBPM readings for participants (not taking antihypertensive medication) will be categorised as per European Society of Cardiology guidelines^21^ into:

Prehypertensive (BP ≥130–134/80–84 mm Hg)Hypertensive (BP ≥135–139/85–89 mm Hg)Normotensive (BP <130/80 mm Hg)

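### The June 2023 close counts 12 weeks from recruitment, but the outcome is timed from birth, so antenatal recruits who give birth after about 7 April 2023 cannot reach week 12

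*Protocol article*

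**What the plan says.** Recruitment and sampling fixes both ends of the calendar. It says "Recruitment will commence in April 2022 until March 2023", and then that "all data collection will cease in June 2023 allowing 12 weeks of BP monitoring from when final participants were recruited in March 2023". The same section describes when women are contacted: "Potential participants will be approached during the antenatal and postnatal period before discharge home". Under Inclusion and exclusion criteria, the qualifying condition is "a diagnosis of new-onset hypertension in pregnancy after 20 weeks gestation and up to 72 hours postpartum".

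The measurements run on a different clock. Home blood pressure monitoring states "Research participants will undergo HBPM every fortnight from week 2 post birth until week 12", and then "At week 12, women will undergo 24-hour ABPM". Data analysis uses the same time origin: the purpose of Objective 1 is "to identify which BP will be used to calculate the rate of persistent hypertension at 12 weeks postpartum", Objective 2 compares home with ambulatory readings at 12 weeks postpartum, and Objective 3 takes persistent hypertension at 12 weeks postpartum as the regression outcome.

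Sample size requires 263 women and targets 300, the difference being for withdrawal and incomplete blood pressure data.

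**The concern.** The end date is justified from recruitment, but every blood pressure assessment is scheduled from birth. The two clocks agree only when recruitment and birth nearly coincide. A woman diagnosed and enrolled during pregnancy may give birth weeks later, and her week 12 moves back by the same interval while the close stays where it is.

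For such a woman the close removes the measurements on which the main results rest: the week-12 home readings behind the rate of persistent hypertension, the ambulatory recording that is the reference for the accuracy analysis, and the outcome for the logistic regression. The loss is administrative and predictable, and it depends on how long before birth she was enrolled. It is therefore not the ordinary dropout that the inflation from 263 to 300 was meant to absorb. Readings not taken before the close cannot be recovered afterwards.

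**Working it through.** **Inputs from the protocol article.** Recruitment ends in March 2023 and data collection ends in June 2023; no day is given for either. Week 12 is counted from birth (84 days). Required sample 263, target 300.

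**1. The stated 12 weeks.** Take the most generous dates. From 31 March to 30 June 2023 is 91 days = 13.0 weeks. Twelve weeks from recruitment therefore fits, with 7 days to spare. The stated figure is right for a woman recruited at or just after birth.

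**2. The same window counted from birth.** Latest birth date = close minus 84 days = 30 June minus 84 days = 7 April 2023. If the three days of home monitoring and the 24-hour recording follow the start of week 12, subtract 4 more days: 3 April. If collection closed on 1 June, the latest birth date would be 9 March.

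**3. A woman recruited on 31 March 2023, assuming birth at 40 weeks.**

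| Gestation at recruitment | Birth | Weeks postpartum on 30 June | Week 12 reached |
|---|---|---|---|
| 39 weeks | 7 April | 12.0 | 30 June |
| 38 weeks | 14 April | 11.0 | 7 July |
| 36 weeks | 28 April | 9.0 | 21 July |
| 32 weeks | 26 May | 5.0 | 18 August |
| 28 weeks | 23 June | 1.0 | 15 September |
| 20 weeks | 18 August | not yet delivered | 10 November |

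Earlier birth shortens the gap but does not close it: a 31 March recruit who gives birth 6 weeks later reaches week 12 on 4 August. Read the other way, with birth at 40 weeks, the latest recruitment date that still reaches week 12 by 30 June is 10 March at 36 weeks' gestation, 10 February at 32 weeks and 13 January at 28 weeks. With birth at 37 weeks, these become 31 March, 3 March and 3 February.

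**4. How many women.** The document gives neither the antenatal share nor the lead from enrolment to birth, so both are assumptions here. With even accrual, intake is 300/52 = 5.77 women per week. A woman with a lead of L weeks is cut off if she is recruited in the last L - 1 weeks, because of the 7 days of slack. Women lost = 5.77 x antenatal share x (L - 1).

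| Lead | 30% antenatal | 50% | 70% |
|---|---|---|---|
| 1 week | 0 | 0 | 0 |
| 2 weeks | 1.7 | 2.9 | 4.0 |
| 4 weeks | 5.2 | 8.7 | 12.1 |
| 6 weeks | 8.7 | 14.4 | 20.2 |
| 8 weeks | 12.1 | 20.2 | 28.3 |

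The range is about 0 to 28. The allowance is 300 - 263 = 37, so the upper end would use 28/37 = 76% of it.

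**5. Effect on precision.** Losing 28 and nobody else leaves 300 - 28 = 272, still above 263. If other losses also use the full 37, then 263 - 28 = 235 remain. The Wald 95% interval width at 20% is 2 x 1.96 x sqrt(0.2 x 0.8/n): 9.7% at 263 and 10.2% at 235, against a target of 10%. The chance of meeting the target falls faster than the width suggests. By exact binomial enumeration with Wilson intervals it is 0.819 at 263 (the stated requirement reproduces) and already 0.525 at 246.

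**The case against.** The strongest reply is that women are said to be approached antenatally, which need not mean that they count as recruited then. If recruitment were completed only after birth, the 12 weeks would be correct. That reading is possible, but nothing in the text states it. The eligibility window is a window for diagnosis and does not settle the moment of enrolment either. If that is the intention, it needs saying. A condensed article may leave cut-offs by due date to the full protocol, but the point here is the reason that the article itself gives for its end date.

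Three stronger readings are tempting, and the document does not support them.

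- *All late antenatal recruits are lost.* They are not. Those who give birth by about 7 April reach week 12.
- *Affected women contribute nothing.* Objective 3 also reports rates at two-week intervals, so a woman cut off at 5 weeks postpartum could still supply weeks 2 and 4. There is one qualification: readings are uploaded when the diary and monitor are returned at 12 weeks postpartum, which for her falls after the close.
- *The estimate is biased by severity.* A long lead implies earlier diagnosis, and severity is a planned factor in the regression, but no passage links lead time to severity or to persistence. Women with the same lead who were recruited earlier in the year are kept: at an 8-week lead, about 7 of 52 weeks' intake (13%) is affected. Loss that depends only on calendar date and on covariates in the model would not by itself bias the regression coefficients.

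It is also fair that the effect on precision is modest when this is the only loss.

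**Conclusion.** The stated basis for the close is wrong for any woman enrolled more than about a week before birth at the end of recruitment. This follows from the document's own dates and schedule. On the most generous dates, giving birth by about 7 April 2023 is the condition for reaching week 12; an earlier close in June makes the condition stricter.

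The size is uncertain. About 0 to 28 women would be affected, assuming even accrual of 300 over 52 weeks, antenatal shares of 30-70% and leads of 1-8 weeks. At the lower end nothing is lost. At the upper end most of the allowance for withdrawal and incomplete data goes to an avoidable cause. A reader might infer that the precision target is sure to fail or that the prevalence estimate is biased; neither is shown. What can be said is that the loss concentrates on women enrolled longest before birth and could tilt the week-12 sample.

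**What to change.** State that data collection ends 12 weeks after the last participant's birth, plus the days needed for the week-12 home and ambulatory monitoring. This removes both the loss and the selection. The cost is one sentence and an extension set by the longest lead. For a lead of 8 weeks from 31 March, week 12 falls on 18 August 2023, which is 49 days or 7 weeks after 30 June, plus about 4 days of measurement. Longer leads would need more.

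If the June 2023 close is fixed, restrict antenatal enrolment in the closing months to women expected to give birth in time to complete week 12 before it (by about 7 April for a 30 June close, or about 3 April with the measurement days). Acknowledge that this excludes women with a longer lead to birth in the final weeks of recruitment. Enrolling them after birth instead does not help, since recruitment itself ends in March 2023. This option protects the numbers but not the representativeness of the late intake.

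If antenatally approached women are in fact recruited only after birth, say so in Recruitment and sampling.

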### Sample size

To obtain an accurate estimate of persistent hypertension rate after birth, a sample size of 263 women with a history of HDP are required. The target sample size is 300 women to compensate for study withdrawal and incomplete BP data. This is based on the anticipated rate of persistent postpartum hypertension of approximately 20% and the corresponding width of 95% CI to be 10% as desired level of precision, with 80% probability of achieving such precision. Considerations were also given to the sample size required to assess agreement between HBPM and ABPM.

### Inclusion and exclusion criteria

Eligible research participants will require a diagnosis of new-onset hypertension in pregnancy after 20 weeks gestation and up to 72 hours postpartum. Research participants in whom English is not their primary spoken language must demonstrate evidence of the ability to communicate any abnormal BP readings with their healthcare provider.

### Patient and public involvement

The patient and public involvement (PPI) steering group includes four women from different ethnic groups including black Caribbean, Asian and white British and European, with a lived experience of HDP who were all involved in discussions related to research priorities and the development of the proposed research study to address priority questions. The PPI group experienced a range of BP disorders during pregnancy including pre-existing hypertension, pre-eclampsia and gestational/postnatal hypertension. This diverse mix of service user backgrounds and experiences ensured that the research team can gain insight into how women prioritise their physical and mental health and well-being after birth, and extent to which this may be influenced by their ethnic and cultural backgrounds.

The PPI group have reviewed the research protocol and all research materials (participant information leaflet, consent forms, questionnaires, posters and BP monitoring instructions, study diary), which were revised to reflect their preferences including how information was structured and ensuring language used is suitable for a lay audience. The PPI group have informed the researcher on all stages of the research project since inception, with financial remuneration for their input and time made in line with the National Institute of Health Research guidance.

### Data collection

#### Home blood pressure monitoring

Research participants will undergo HBPM every fortnight from week 2 post birth until week 12 as per a HBPM protocol based on that used by Alemida *et al*. Women will take three BP readings in the morning, early afternoon and in the evening, a total of nine BP readings per day, for three consecutive days.^17^ At week 12, women will undergo 24-hour ABPM (figure 1).

**Figure 1 F1:**
[figure not shown]
Overview of participant blood pressure (BP) monitoring protocol. ABPM, ambulatory blood pressure monitoring; HBPM, home blood pressure monitoring.

HBPM will be undertaken using Microlife Watch BP Home as they have been validated for pregnancy and pre-eclampsia.^18^ Participants will record their BP measurements manually in a diary provided by the research team. Participants will receive guidance on what to do if they discover BP outside the normal range. Local research midwives at each study site will upload the BP measurements directly from the BP monitor into an electronic file on return of the BP diaries and monitor at 12 weeks postpartum.

#### Ambulatory blood pressure monitoring

Ambulatory BP monitoring will be undertaken using Mobil-O-Graph as this monitor is endorsed by the British and Irish Hypertension Society and has been validated against the European Society of Hypertension criteria.^19 20^ The study site research midwives will upload the 24-hour BP analysis to a password-protected excel file.

#### Questionnaires

Questionnaire 1 will be distributed online at 8 weeks postpartum to assess if participants had a postnatal GP review and self-report on what occurred at this appointment if applicable. Part 2 of the questionnaire will assess participants’ risk perception of CVD development and emotional well-being following a pregnancy with HDP.Questionnaire 2 will be distributed at 12-week post partum assessing participants’ views on their experience of HBPM and ABPM (figure 2).A questionnaire aimed at clinicians involved in the care of postpartum women with a HDP will be distributed to midwives, obstetricians and GPs assessing their knowledge on HDP and associated risk of CVD. In addition, a focus group with GPs will provide insight to the postnatal GP check from a clinician’s perspective.

